### Data collection

After consenting to take part in the evaluation research study, patient participants will be allocated a unique study ID number and complete baseline measures. Participants will be asked to provide their email address, postal address and contact number for data collection purposes. They will be sent a link in an email to a web-based case report form which will host the data collection measures. The data entered into this form will be anonymous and only linked to the patient by the unique ID number. Participants will be asked to complete socio-demographic information at baseline and self-report measures at baseline, 3 months and 12 months. Socio-demographic information will be collected to describe the sample, and to compare intervention use and self-report measure data.

Both patient and health professional participants will be asked to take part in semi-structured interviews. Each participant may be interviewed several times throughout the course of the study. We will sample until saturation is reached. In order to capture a breadth of experiences interviews will be conducted with patients from a range of ethnic backgrounds, ages, socio-demographic statuses, length of time with diabetes, treatment types, and associated complications, as well as a range of experience with computers and the internet. Similarly, to capture a range of staff experiences, we will seek to interview consultants, salaried doctors, junior hospital doctors, general practice partners, general practice managers, practice nurses, community nurses, hospital diabetes nurses and reception staff from GP surgeries and diabetes clinics. It is likely that there will be different levels of engagement with *HeLP-Diabetes* and with the evaluation research study between different members of staff and between different services and sites. Therefore, not all interviews will be face to face; initial interviews and follow-up encounters with some participants may be short, highly focused telephone interviews. These will minimise the demand on participants, and is likely to be much more cost effective. However, more in-depth, semi structured interviews will be conducted with participants wherever possible. Participants may be sampled purposefully at times to ensure that we have captured a range of experiences and opinions.

Data on intervention use will be recorded automatically by the intervention software and Google Analytics and will be downloaded into a spread sheet. Data on the type of GP surgeries and diabetes clinics that take up *HeLP-Diabetes* will be collected from Population Manager Data, Public Health Observatories [21] data and a data collection form to be completed by the Practice Manager or Clinic Lead at each site. The time spent by individuals involved in the implementation of *HeLP-Diabetes* will be recorded on a proforma.

### Anaylsis

The proportion of GP surgeries and clinics offered *HeLP-Diabetes* who adopt it, the number of patients who register on *HeLP-Diabetes*, the socio-demographic characteristics of the patients who take part in the evaluation study and the characteristics of the clinics and GP surgeries that adopt *HeLP-Diabetes* will be described using descriptive statistics. SPSS statistical software [24] will be used for coding and analysing these data. Descriptive statistics will also be used to explain how patients make use of *HeLP-Diabetes* including counts of pages accessed, number of logins, the times of use, the duration of use and the patterns of use by different users. This data will be recorded automatically by the website software. The time and other resources expended on implementing *HeLP-Diabetes* will be recorded on a proforma and these will be collated on a spread sheet and data described descriptively.

The cost of health professional input from the GP surgeries and clinics will be based on national average rates using Personal Social Services Research Unit estimates. Estimates of the additional time required from the general practice and clinic staff where *HeLP-Diabetes* is implemented will be calculated from responses in the qualitative interviews. Resources required in training individual patients to use *HeLP-Diabetes* will be estimated.

Participant scores on the PAID and DSMSE-UK scales will be compared statistically at the different time points using a repeated measures analysis of variance test using time as the independent variable. If a statistically significant effect is found post-hoc tests will be used to explore this further. Follow up PAID and DSMSE-UK scores will be adjusted for initial scores and other baseline covariates including age, gender, and duration of diabetes. Group effects including gender and age will be assessed using mixed-between within subjects analysis of variance.

With respondents’ consent, all semi-structured interviews will be audio-recorded, transcribed (and edited to ensure anonymity of respondent) and data will be subjected to formal analysis. Patient and staff interviews will be analysed inductively to identify themes and categories, a process of constant comparison will be used to establish analytical categories. Atlas. ti [25] data collation and management software will be used to aid data management and analysis.

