### Setting

The study will be conducted in GP surgeries, community diabetes clinics and hospital based diabetes clinics within two inner city London boroughs: There are approximately 80 GP surgeries, two services providing a range of community diabetes clinics and three hospitals running diabetes clinics within these two boroughs. Our aim is to make *HeLP-Diabetes* available to up to 30 GP surgeries and all diabetes clinics. Within these boroughs there are 16,223 people on GP registers with a recorded diagnosis of diabetes [21]. Since T2DM accounts for 90% of all diabetes cases, there are up to 14,601 potential users of *HeLP-Diabetes* within these two boroughs.

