### Implementation plan

An implementation plan has been devised by the research team which will be offered to all services. This plan includes the following steps; an initial meeting at the GPsurgery or clinic to explain the new *HeLP-Diabetes* service, a demonstration of *HeLP-Diabetes*, training for staff who will be using *HeLP-Diabetes* top-up training and support as necessary, training patients to use *HeLP-Diabetes*, follow up contact with patients, continued monitoring and feedback to staff, and the provision of training materials to staff and patients. Each GP surgery and diabetes clinic will be invited to work with researchers to tailor the implementation plan to the individual setting.

The researcher will spend time with staff to implement *HeLP-Diabetes* and to provide support and facilitate patient training appointments. Formal feedback from interviews with staff and patients and informal feedback such as lessons learned from training staff and patients will be used by the researcher to develop and refine the implementation procedures. The iterative design will allow the implementation plan to be tested out on a small scale, the researcher to learn from the experience and modifications to be made to plan before testing it on a another small number of services. This method will allow for difficulties and challenges to be explored and addressed, which may otherwise be missed by widespread implementation. Through the process of modifying the implementation plan based on feedback from patients and staff and by allowing the implementation plan to be tailored to individual sites, we hope to increase buy-in and ownership of *HeLP-Diabetes* by staff and reduce barriers to successful implementation.

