Patient participants will be asked to complete two self-report measures. The first will be the Problem Areas in Diabetes (PAID) scale [22] which is a health related quality of life and emotional distress measure. It is comprised of 20 items focusing on areas that cause difficulty for people living with diabetes including; social situations, food, friends and family, diabetes treatment, emotions, relationships with healthcare professionals and social support. The second measure will be the Diabetes Management Self-Efficacy Scale (DMSES-UK) [23] which measures the individual’s efficacy expectations for engaging in 20 diabetes self-management activities, for example, taking daily exercise and keeping to a healthy eating plan when away from home. A sample size of 100 patients will detect a 3.5 point difference in the mean PAID score from baseline and a 9 point difference in the mean DMSES score from baseline. These calculations are based on 90% power (α = 0.05).

Additional self-report measures may be introduced to new cohorts of patients in order to test developing hypotheses generated by interviews with patients and staff. For example, if a theme emerges from the interviews suggesting that using *HeLP-Diabetes* may increase patients’ levels of physical activity, we may administer a physical activity self-report measure to a new cohort of patients at baseline, 3 months and 12 months to quantitatively explore this. Power and sample size will be calculated for each new measure prior to it being administered.

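### The PAID and DMSES analysis and the 100-patient power statement name no allowance for clustering by service; if change varies between services, standard errors are too small and power is below 90%

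*Protocol article*

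**What the plan says.** The analysis section of the Protocol article states that PAID and DMSES scores "will be compared statistically at the different time points using a repeated measures analysis of variance test using time as the independent variable". The same paragraph adds post-hoc tests after a significant result, adjustment of follow-up scores for initial score, age, gender and duration of diabetes, and a mixed between-within analysis of variance for group effects such as gender and age. Service or site appears in none of these.

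Under Outcomes, objective (d), the planned number is 100 patients, and the article states that this number "will detect a 3.5 point difference in the mean PAID score from baseline". For DMSES the corresponding change is 9 points. It adds only "These calculations are based on 90% power" and α = 0.05. No SD, baseline-to-follow-up correlation, ICC or design effect is stated.

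The Setting section intends to make the programme "available to up to 30 GP surgeries and all diabetes clinics", and counts two community services and three hospitals that run clinics. The Procedure section brings sites in two or three at a time, so that later sites benefit from earlier ones. The Implementation plan section says: "Each GP surgery and diabetes clinic will be invited to work with researchers to tailor the implementation plan to the individual setting". The Data collection section expects engagement to differ between services and sites.

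**The concern.** Repeated measures ANOVA allows for correlation between the scores of one patient. It takes different patients as independent. Here, the version of the plan, the local tailoring and the engagement of staff are shared by the patients of one service. They act after baseline, so they could affect how much patients change as well as where they start. If they do, changes within a service are positively correlated and the usual standard error of mean change is too small. Confidence intervals would then be too narrow, a nominal 5% test would reject too often, and 100 patients would carry less information than the power statement suggests. A significant time effect triggers the post-hoc tests, and the abstract says that patient benefits will be reported, so the standard errors matter even for an exploratory objective.

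**Working it through.** **Inputs from the article.** N = 100; detectable change 3.5 (PAID) and 9 (DMSES); power 90%; α = 0.05, taken as two-sided because sidedness is not stated; at most 30 + 2 + 3 = 35 services.

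**Assumed, because the article gives no value.** ICC of the change score 0.02 to 0.10; 10 services as an illustration of fewer contributing services; coefficient of variation (CV) of patients per service 0 or 0.7.

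**Step 1: the plan's own figure.** For a paired mean change, n = ((1.960 + 1.282) × SD / Δ)². N = 100 cannot be reproduced without an SD. Solving for the SD of change gives:
- PAID: 3.5 × 10 / 3.242 = 10.8
- DMSES: 9 × 10 / 3.242 = 27.8

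Both correspond to a standardised change of 0.324. The two targets therefore agree with one plain paired calculation on independent patients. That does not prove this was the calculation used.

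**Step 2: design effect.** DE = 1 + ((CV² + 1) × m − 1) × ICC, with m = 100 / number of services. Then:
- standard error multiplier = √DE
- power = Φ(3.242/√DE − 1.960)
- true level of the naive 5% test = 2 × (1 − Φ(1.960/√DE))

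Example with 10 equal services and ICC 0.10: DE = 1 + 9 × 0.10 = 1.90; √1.90 = 1.38; power = Φ(2.352 − 1.960) = 65%; true level = 15.5%.

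| Services | CV | ICC | DE | SE × | Power | True level |
|---|---|---|---|---|---|---|
| 35 | 0 | 0.02 | 1.04 | 1.02 | 88.9% | 5.4% |
| 35 | 0 | 0.05 | 1.09 | 1.05 | 87.3% | 6.1% |
| 35 | 0 | 0.10 | 1.19 | 1.09 | 84.5% | 7.2% |
| 35 | 0.7 | 0.05 | 1.16 | 1.08 | 85.2% | 6.9% |
| 10 | 0 | 0.02 | 1.18 | 1.09 | 84.7% | 7.1% |
| 10 | 0 | 0.05 | 1.45 | 1.20 | 76.8% | 10.4% |
| 10 | 0 | 0.10 | 1.90 | 1.38 | 65.2% | 15.5% |
| 10 | 0.7 | 0.05 | 1.70 | 1.30 | 70.2% | 13.2% |

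At ICC 0 nothing changes. Using a standardised change of 0.327, the value from a t-based calculation, raises power by less than one percentage point (66.0% in place of 65.2% in the worst equal-size row).

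**Step 3: which service term works.** Write a patient's score as service level + patient level + time effect + error. In follow-up minus baseline the service level cancels, so a random service intercept alone leaves the standard error of change as it was. Only a service effect that varies with time (site-by-time) enters change. In a model for the follow-up score adjusted for baseline, nothing is subtracted in this way. There a random service effect captures the between-service variation that remains after adjustment.

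**The case against.** The strongest reply is that everything rests on the ICC of change. Stable differences between services cancel in within-patient change. One common plan is offered to all services, which are merely invited to adapt it, and the training appointment is tailored to the patient. Variation in change between services is therefore plausible but not established. This stands, and it is why the point is conditional. A reader might infer from the tailoring that intervals are certainly too narrow and that 90% power is certainly missed. The article does not support that.

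Second, at the full 35 services, with about 2.9 patients each, the loss is small. This also stands. But 35 is a ceiling: services may decline the programme or opt out of the evaluation, and the article does not say how the 100 patients will be spread.

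Third, the article is condensed, its covariate and group-effect lists are open-ended, and the sample-size statement gives no SD. A reader might infer that independence was assumed, but that would be an inference from silence: an allowance for clustering can be neither shown nor excluded. What remains is that the test and its factor are stated, and no service term is among the terms named.

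Fourth, a reader might conclude that a random service intercept never helps. That is true for within-patient change, but wrong for the baseline-adjusted follow-up analysis that the article also names.

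Fifth, registration records the surgery or clinics attended, so a patient may belong to more than one service. Learning also passes between batches, a level that clustering on service does not capture. Both are fair. The first is handled in the fix; the second remains a limitation.

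Finally, the objective is exploratory, in a cohort that runs alongside a randomised trial, so no confirmatory decision depends on this test. That limits the weight of the point but does not make the standard errors right.

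**Conclusion.** The point holds conditionally. The named analysis has no service term, and the power statement names no allowance for clustering, in a study where the intervention is delivered and adapted service by service. If change varies between services, the standard errors are too small and power is below 90%.

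The size depends on the assumed ICC of 0.02 to 0.10 and on the number and balance of contributing services. With 35 equal services it is minor: a loss of about 1 to 5 percentage points of power. With about 10 services it is material: a loss of about 5 to 25 points, with a true level of up to about 16%. The worst of these figures needs both 10 services and an ICC of 0.10, and should not be read as the expected result. This is a worthwhile, inexpensive improvement to an exploratory analysis.

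**What to change.** - For within-patient change in PAID and DMSES, fit a random site-by-time effect, or use standard errors clustered on service with a small-sample correction. A site intercept alone is not enough here.
- For baseline-adjusted follow-up scores, add a random service effect.
- Assign each patient to one service by a rule fixed in advance, for example the service that referred them for training.
- Either state that the 90% power is conditional on independent patients, or restate it with the assumed SD of change, ICC and expected number of services.

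**Cost.** A few lines of wording. The surgery or clinics attended are already recorded at registration, so only the assignment rule is new. The honest price is wider intervals: about 2 to 9% with 35 equal services, and 9 to 38% with 10 over the same ICC range. The stated power becomes less favourable.

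No extra patients are asked for, and the change corrects the standard errors without restoring lost power. At the extreme, more patients from the same services could not restore it. With 10 services and ICC 0.10 the effective sample size stays below 10 / 0.10 = 100 however many are recruited. The objective stays exploratory.

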### Procedure

The use of *HeLP-Diabetes* will be offered to GP surgeries and diabetes clinics free of charge for the duration of the study (30 months). *HeLP-Diabetes* will be made available to batches of GP surgeries and clinics (approx. 2 or 3 at a time). This will allow learning and experience gained from the implementation at each batch of sites to be transferred to subsequent ones. Once organisations have agreed to use *HeLP-Diabetes* they will be asked to opt-in to the research evaluation study. Organisations who opt-out of the research evaluation will still be free to use *HeLP-Diabetes* without participation in the research.

Staff working in services that agree to use *HeLP-Diabetes* will be asked to recommend its use to all suitable patients with T2DM and refer them to a training appointment with a researcher or a member of the clinical team. Suitable times to recommend the use of *HeLP-Diabetes* may include at annual diabetes reviews and when a patient is newly diagnosed. Staff will also be encouraged to maintain engagement with *HeLP-Diabetes* by encouraging patients to use it at appropriate times during routine consultations.

During training appointments patients will be registered on the *HeLP-Diabetes* site and shown how to use it. Each appointment will be tailored to the specific needs of the patient and will focus on an aspect of diabetes self-management important to the patient. At the end of the training appointment patients will be invited to take part in the research study evaluating the implementation of *HeLP-Diabetes*. Patients who agree to take part in the evaluation study will be asked to sign a consent form after reading the participant information sheet and having the opportunity to ask any questions. Patients who opt-out of the research evaluation will still be free to use *HeLP-Diabetes* without participation in the research.

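### The repeated measures ANOVA keeps only patients with all three questionnaires and has no site term; a likelihood-based mixed model would use every returned score

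*Protocol article*

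**What the plan says.** All of this is in the protocol article.

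- **Main comparison (Analysis).** PAID and DMSES-UK scores at the different time points are compared "using a repeated measures analysis of variance test using time as the independent variable", with post-hoc tests if the time effect is significant.
- **Adjustment (Analysis).** Follow-up "scores will be adjusted for initial scores and other baseline covariates including age, gender, and duration of diabetes".
- **Subgroups (Analysis).** "Group effects including gender and age will be assessed using mixed-between within subjects analysis of variance".
- **Timing and mode (Data collection).** Participants complete "self-report measures at baseline, 3 months and 12 months". On how: "They will be sent a link in an email to a web-based case report form which will host the data collection measures".
- **Sample size (Outcomes).** "A sample size of 100 patients will detect a 3.5 point difference in the mean PAID score from baseline". For DMSES the corresponding figure is 9 points. Both are at 90% power and α = 0.05. No standard deviation and no allowance for non-return is given.
- **Sites (Setting, Procedure, Implementation plan).** Up to 30 GP surgeries and all diabetes clinics in two boroughs (two community services, three hospitals). They join in batches of about two or three, with an implementation plan tailored to each site and revised between batches.
- **Duration (Procedure).** The intervention "will be offered to GP surgeries and diabetes clinics free of charge for the duration of the study (30 months"). The article does not say when patient enrolment closes or whether follow-up ends at month 30.

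**The concern.** Classical repeated measures ANOVA needs a complete row for each patient. Someone who returns baseline and 3 months but not 12 months contributes nothing, not even to the 3-month comparison. The mixed between-within ANOVA works the same way; despite its name it is not a likelihood-based mixed model.

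Missing waves are likely when questionnaires arrive by email over a year, and patients who stop using a website may also stop answering its questionnaires. The cohort has no control group, so any distortion from selective return passes straight into the reported change. Patients enrolled too late to reach 12 months, if there are any, would also lose their baseline and 3-month scores from the ANOVA. They would have had the most developed implementation plan.

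Finally, patients are nested in sites whose implementation differs by design, yet no site term is named. If change varies between sites, the standard errors will be too small.

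**Working it through.** **1. The plan's own figure.** The sample size of 100 cannot be reproduced because no standard deviation is given. It can only be inverted. For a paired mean change with a two-sided test, n = (SD × (1.960 + 1.282) / δ)², so SD = δ × √100 / 3.2415.

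- PAID: 3.5 × 10 / 3.2415 = 10.8.
- DMSES: 9 × 10 / 3.2415 = 27.8.

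Both imply the same standardised change, 0.324, so the two statements agree with each other.

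**2. Power when only complete patients are used.** Power = Φ(0.3242 × √n − 1.96), where n is the number with all three scores out of 100 enrolled. Completion rates are assumptions.

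| Complete | 0.3242 × √n | Power | Enrolment for 100 completers |
|---|---|---|---|
| 100% | 3.242 | 90% | 100 |
| 90% | 3.075 | 86.8% | 112 |
| 80% | 2.899 | 82.6% | 125 |
| 70% | 2.712 | 77.4% | 143 |
| 60% | 2.511 | 70.9% | 167 |
| 50% | 2.292 | 63.0% | 200 |

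**3. Bias, and what a mixed model does about it.** Simulation of 4,000 cohorts of 100: true change −3.5 at both visits, change SD 10.8, correlation 0.6, about 60–64% complete. The correlation and the non-return mechanisms are assumptions. Entries are the mean estimated change at 3 / 12 months.

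| Non-return depends on | Complete cases | Likelihood, all data |
|---|---|---|
| Nothing (random) | −3.50 / −3.52 | −3.52 / −3.52 |
| Random loss of the 12-month score only, as with truncation by entry date | −3.51 / −3.48 | −3.50 / −3.47 |
| Baseline score | −1.87 / −1.88 | −3.49 / −3.50 |
| 3-month score (12-month loss) | −4.62 / −3.53 | −3.52 / −3.53 |
| The unseen score itself | −4.16 / −4.55 | −4.69 / −5.51 |

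A second simulation (3,000 cohorts, score SD 15, change SD 10.7) made 12-month loss more likely after less improvement at 3 months: log-odds 0.5–1.0 per SD, 26–50% lost. The complete-case 12-month change was −4.2 to −5.7 against a true −3.5, and −0.7 to −2.2 against a true 0. The likelihood estimate stayed at −3.5 and 0.

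The precision gain under random loss is larger at 3 months than at 12. The SD of the estimate falls from 1.36 to 1.14 at 3 months, and from 1.38 to 1.31 at 12 months. The mixed model recovers discarded 3-month scores; it cannot recover 12-month scores that were never returned.

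**4. Late enrolment.** A 12-month score by month 30 needs enrolment by month 18. If follow-up did stop at month 30 (assumption), the share of patients without a 12-month score under uniform enrolment would be:

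- enrolment to month 18: 0%;
- to month 24: (24 − 18) / 24 = 25%;
- to month 30: (30 − 18) / 30 = 40%.

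**5. Site.** Upper bound on sites: 30 + 2 + 3 = 35, so 100 / 35 ≈ 2.9 patients per site. With an assumed intraclass correlation of change of 0.05, the design effect is 1 + (2.857 − 1) × 0.05 = 1.093, and power = Φ(3.2415 / √1.093 − 1.96) = 87%. Ten patients per site would give 1 + 9 × 0.05 = 1.45 and 77%, but that means ten sites for 100 patients, or 350 patients in 35.

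A random site intercept alone does not address this, because it cancels from within-patient change. For 10 sites of 10 patients, change SD 10.7 and intraclass correlation 0.05, the naive standard error is 10.7 / √100 = 1.07 and the correct one is 1.07 × √1.45 = 1.29. In 60 simulated two-wave cohorts a random-intercept model gave a mean of 1.06.

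**The case against.** - **This is a condensed article, and rules for missing data commonly sit elsewhere.** True, and the absence of such a rule is not the point. Exclusion of incomplete patients is inferred from the named method. That method is fixed here, and a better one is available.
- **A reader might infer that every patient from a late batch is dropped.** The documents do not support this. The 30 months is the study duration and free-use period; no enrolment close or follow-up cut-off is stated, and the 100 patients could be enrolled early. The affected share could be zero. Loss by entry date alone also leaves the estimate unbiased if change is unrelated to entry date, although a plan revised between batches means that cannot be presumed.
- **A reader might infer that the ANOVA estimates are biased.** They are at risk of bias under some mechanisms and unbiased under others. The likelihood model removes the bias only when data are missing at random. When loss depended on the unseen score it did worse than complete cases (−5.51 against −4.55 at 12 months, true −3.5).
- **The covariate-adjusted follow-up analysis may keep patients with only one follow-up.** This stands. Nothing says it requires both, so the loss of data is a statement about the two ANOVAs.
- **Age as a grouping factor is inferred.** Age is also listed as a covariate. The between-within ANOVA treats it as a group effect, but no categories are given and no loss can be quantified.
- **The objective is exploratory.** This lowers the stakes: uptake, barriers and resources are unaffected. Even so, power is claimed formally, and the abstract undertakes to report patient benefits.

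**Conclusion.** The point holds in a limited form. The named ANOVAs, in classical form, set aside the returned scores of any patient with a missing wave and take no account of site. Power falls from 90% to about 83% at 80% completion and about 71% at 60%; these rest on assumed completion and on the change SD implied by the sample size statement. Bias is conditional on non-return being related to scores. In the scenarios examined it ranged from none to about 2 points, against a target difference of 3.5, at 12 months; the 3-month estimate can also be affected.

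The site issue is secondary. It concerns standard errors only, and at about 3 patients per site costs roughly 3 percentage points of power at an assumed intraclass correlation of 0.05. Fewer sites with more patients each would raise that cost. The change is worth making because it is inexpensive, not because the planned result is known to be wrong.

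**What to change.** Replace both ANOVAs with a likelihood-based linear mixed model, which SPSS also offers:

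- include all patients with at least one score;
- fit time as a categorical factor with an unstructured within-patient covariance;
- fit age as continuous with a time-by-age term, and gender with a time-by-gender term;
- allow for site clustering of change through a random site-by-time effect or site-clustered standard errors, not a site intercept alone;
- state that the model assumes data are missing at random;
- add a sensitivity analysis for data missing not at random, for example shifting the unseen scores over a stated range to find where the conclusion changes;
- keep the complete-case ANOVA as a secondary check only.

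Any patients enrolled too late for a 12-month score would then still contribute their baseline and 3-month data. The cost is a few sentences of analysis text and slightly more analysis work, with no new data or patients. The drawback is reliance on the missing-at-random assumption, which is why the sensitivity analysis is part of the change.
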